##### Additional exploratory analysis

The exploratory analyses include analysis of biomarkers in urine and plasma and the evaluation of these biomarkers in relation to renal prognosis. Renal biopsies form the included patients will be systematically re-evaluated to identify possible renal prognostic factors. The re-evaluation will include the presence and quantification of eosinophilic granulocytes, degrees of inflammation and fibrosis and additional staining for special biomarkers such as TGF-β1 and BMP-7. Safety end-point such as development of diabetes mellitus, infection rate, hospital admission and death will be explored.

## Methods

The local investigators are responsible for patient recruitment, clinical follow up, data entry in Redcap and shipment of centrally analyzed biochemical samples (biomarkers).

Blood and urine from biochemistry A, biochemistry B, 24-h urine collection and spot urine A, are analyzed at the local clinical biochemistry laboratory using standardized automated procedures. The CKD-EPI formula is used to calculate eGFR [47]. Similar, standardized and national reference intervals are applied by all clinical biochemistry laboratories in Denmark.

Blood sample C and spot urine B are analyzed at The University Clinic of Nephrology and Hypertension, Gødstrup Hospital using commercially available assays based on ELISA or RIA methods. Samples are centrifuged and frozen locally at − 80 °C, shipped to the central lab and stored in a research biobank at − 80 °C, until analyzed. Supplementary analyses of the material not described in the protocol is subject to additional approval by the scientific ethics committee.

Quality of life is estimated with the SF-36 questionary which the patients fill in 4 times during the study period [48, 49].

Safety estimates are evaluated in several ways. This includes the frequency of side effects, adverse events and hospital admissions, which are reported continuously by treating physicians in the eCRF. Development of diabetes in estimated by momentary and long term blood glucose levels (Hemoglobin A1c) and new onset hypertension from the blood pressure levels and medical chart reported in eCRF.

### Pathology

Renal biopsies forming the basis for the diagnosis and patient inclusion are performed at the local pathology services. The histological diagnosis of AIN is based on the finding of inflammatory cells in the renal tissue, primarily in the interstitium and possibly in the renal tubules, while blood vessels and glomeruli are spared [7, 15, 18].

Subsequently, all biopsies are evaluated and scored by the Dept. of Pathology, Odense University Hospital. A complete analysis plan is under development, but the evaluation should involve the staining for inflammation, fibrosis and tubular damage markers, including TGF-β1, BMP-7, A1M, B2M, MCP-1, NGAL, NAG, IL-18, TIMP-2, KIM-1 and IGFBP7.

### Statistics

The primary analysis will be performed as “intention to treat”, and the secondary analysis as “treated as”. Normally distributed variables are compared by unpaired t-test or one-way ANOVA. Repeated measures are analyzed using a general linear model (GLM). Comparable non-parametric tests are used in case of non-normally distributed variables. Both absolute and relative proportions are analyzed. Secondary end-points are analyzed as differences in absolute or relative proportions. Analysis of factors affecting the primary end-point will be performed using a GLM. Kaplan Meier curves will be used when appropriate e.g. in the evaluation of time to end stage renal failure. Any correlation between the primary end point and relevant secondary outcomes and outcomes form the exploratory analysis will be evaluated with appropriate adjustment for potential confounders.

Sample size was estimated for the primary outcome based on a clinical relevant 10 ml/min/1.73m^2^ difference in renal function (eGFR, CKD-EPI) between groups at 3 months, a standard deviation of 18 ml/min, a power of 0.80 and a significance level of 0.05. This showed that 51 patients should be included in each group. Anticipating dropouts, we estimate that 55 patients in each group are necessary and plan to randomize 110 patients.

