## Background

Acute renal failure is associated with greatly increased mortality and morbidity irrespective of its cause [1, 2]. Acute interstitial nephritis (AIN) is an important and common cause of acute renal failure and occurs in 13–27% of renal biopsies performed in acute renal failure requiring dialysis in 40% of cases [3–6]. Histologically AIN is characterized by peritubular inflammation while glomeruli and vessels are typically spared [7]. Although some patients recover renal function completely, as many as 30–70% do not fully regain renal function leading to chronic kidney disease (CKD) [6, 8–14]. CKD is associated with increased morbidity and mortality. Two recent studies suggested that the risk of end stage renal disease requiring dialysis after biopsy proven AIN is 5–7% [6, 13].

In addition to renal failure AIN may present with joint pain (45%), fever (36%), skin rash (22%), eosinophilia (35%), microscopic hematuria (67%), macroscopic hematuria (5%), leukocyturia (82%), non-nephrotic proteinuria (93%), nephrotic proteinuria (3%) and nephrotic syndrome (1%) [15]. AIN can be subdivided in 3 categories based on the precipitating cause: drug induced (75%), infection (5–10%) or autoimmune diseases (15–20%) [5, 7, 16–18]. The pathophysiological mechanisms leading to renal inflammation in AIN are not fully clarified. Fibrotic changes can be observed 7–10 days after the beginning of the inflammatory process and if the triggering cause is not eliminated, the inflammation may proceed to interstitial fibrosis, tubular atrophy and chronic renal failure [19]. Studies have shown that macrophages, lymphocytes and activated tubular cells produce various cytokines that stimulate proliferation of fibroblast cells leading to fibrosis [20, 21]. Transforming growth factor-β1 (TGF-β1) promotes fibroblast activity in vitro and alters the phenotype of mesangial cells to a more fibroblast-like phenotype [22, 23]. Transgenetic mice overesxpressing TGF-β1 show increased renal fibrosis [24, 25]. Thus, TGF-β1 appears to play a central role in the development of renal fibrosis [26]. Bone morphogenetic protein-7 (BMP-7), on the other hand is a natural antagonist of TGF-β1 with anti-fibrotic and anti-inflammatory properties [26]. The roles of TGF-β1 and BMP-7 in AIN; however, have not been elucidated.

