There are no generally accepted guidelines for the treatment of AIN [27], but normally this would include elimination of the precipitating cause and stimulus leading to renal inflammation. Since AIN is characterized by an enhanced immune response, immunosuppressive treatment could potentially improve prognosis by attenuating inflammation and subsequent fibrosis. Case series have suggested positive effects of steroid treatment, but only few larger, retrospective registry based studies have examined this [6, 8, 9, 12–14, 19, 28]. At present, only three retrospective studies with more than 100 patients have been published [29–31]. Muriithi and colleagues identified 133 cases with AIN, of which 95 were drug-induced [31, 32]. The study showed no difference in renal function after 1, 3 and 6 months when comparing 83 steroid-treated with 12 non-steroid-treated patients. In steroid-treated patients, a longer time from the onset of symptoms or biopsy to the initiation of steroid treatment was associated with inferior restoration of renal function. A retrospective, Scottish study including 171 cases of drug-induced AIN also failed to demonstrate an effect of steroid treatment on renal function after 12 months of follow-up [30]. As in the previous study, the steroid-treated (*n* = 124) had higher baseline creatinine levels. In contrast, a recent study from England including 187 patients showed a possible positive effect of steroid treatment [29]. After 24 months, eGFR was 42 ml/min in the steroid-treated group versus 24 ml/min in non-steroid-treated patients. In addition, there was a tendency towards fewer patients requiring of dialysis after 24 months among those treated with steroid. Baseline renal function was comparable among the steroid- and non-steroid-treated patients. Interestingly, a sub-analysis including only patients with drug-triggered AIN, i.e. excluding patients with autoimmune disease, did not show any significant effect of steroid treatment. This indicates that steroid treatment may only benefit patients with autoimmune related AIN. Retrospective studies are hampered by selection bias and there are no published, prospective, randomized studies evaluating the effects of steroids in AIN leaving the use of steroids in AIN controversial. Steroid treatment has several physical and mental adverse effects, such as diabetes mellitus, hypertension, cataract, osteoporosis and manic episodes and is associated with hyperlipidemia, obesity and osteonecrosis [33]. Despite the limited evidence of effects of steroids and potential adverse effects, prednisolone is frequently used in the treatment of AIN and there is a strong need for clinical trials on the effects of immunosuppression, including steroids, in the treatment of AIN.

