#### Randomization

Randomization is performed locally and electronically using REDCap (www.redcap.au.dk; Clinical Trial Unit, Aarhus University). Randomization is performed 1:1 in blocks of 6. Since only a few subjects are expected to be included each center, any center effects are considered insignificant. Neither clinicians nor patients are blinded to the study treatment group.

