### Study overview

Overview of the study from inclusion to week 52 is shown in Table 1.

**Table 1 Tab1:** Overview of the study from inclusion to week 52

		Day 0^a^	Day 2	Day 4	Week 1	Week 2	Week 4	Week 8	Week 12	Week 26	Week 52
Treatment	A	No treatment									
	B	Oral prednisolone tapered over 8 weeks									
Medical history		+									
Biochemistry A		+	+	+	+	+	+	+	+	+	+
Biochemistry B		+							+	+	+
Biochemistry C		+			+		+		+		+
Study medication (group B)		+			+	+	+	+			
Blood pressure, HR		+	+	+	+	+	+	+	+	+	+
Clinical examination		+			+	+	+	+	+	+	+
24 h urine		+					+		+		+
Spot urine A		+	+	+	+	+	+	+	+	+	+
Spot urine B		+			+		+		+		+
Questionnaire (SF36)		+					+		+		+

Biochemistry A: P-sodium, p-potassium, p-total calcium, p-ionized calcium, p-phosphate, p-creatinine, eGFR, p-urea, p-glucose, WBC, p-c-reactive protein (CRP), b-sedimentation rate, p-PTH

Biochemistry B: Hemoglobin A1C. p-TSH, p-25-Hydroxy-Vitamine D2 + D3

Biochemistry C: TGF-β1, BMP-7

Study medication: Dose and adverse effects

Clinical examination: Body weight and physical examination

24-h urine collection: Urinary volume and urinary sodium, creatinine, and albumin excretion

Spot urine A: Urine-dip stick (hemoglobin, protein, leucocytes, glucose, nitrite), urinary albumin and creatinine concentrations and urinary albumin/creatinine ratio

Spot urine B: Urinary concentration and ratios in relation to urinary creatinine of TGF-β1, BMP-7, A1M, B2M, MCP-1, NGAL, NAG, IL-18, TIMP-2, KIM-1, IGFBP7 and CD163-

Questionnaire: SF36 is filled in by the patient

^a^Before start of study medication

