### Endpoints

#### Primary

eGFR 3 months after inclusion (eGFR for patients on dialysis at 3 months is defined as “0 ml/min/1.73 m^2^).

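### The only named method that fits the primary comparison is unadjusted, so the precision available from day-0 eGFR is given up

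*Protocol article*

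**What the plan says.** **Endpoint.** Under Endpoints, Primary, the outcome is "eGFR 3 months after inclusion (eGFR for patients on dialysis at 3 months is defined as" zero. It is a single value per patient at one time point.

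**Test.** The Statistics section calls the primary analysis intention to treat. It then says in general terms: "Normally distributed variables are compared by unpaired t-test or one-way ANOVA". The fallback is equally general: "Comparable non-parametric tests are used in case of non-normally distributed variables". No covariate is attached to either sentence.

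**Linear models.** A GLM is named twice, once for repeated measures and once here: "Analysis of factors affecting the primary end-point will be performed using a GLM". Neither is called the comparison of arms, and no covariate is listed. Adjustment for confounders is mentioned only for correlations between the primary endpoint and other outcomes.

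**Allocation.** "Randomization is performed 1:1 in blocks of 6". No stratification factor is named.

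**Baseline data.** Biochemistry A in Table 1 includes "p-creatinine, eGFR, p-urea, p-glucose". It is scheduled at every visit from day 0, and the table's footnote places day 0 before the start of study medication.

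**The concern.** Patients can enter with very different degrees of renal impairment. The inclusion criteria admit a plasma creatinine just above 120 μmol/L or a rise of just over 30 μmol/L, and acute dialysis is not among the exclusions. To the extent that day-0 eGFR predicts 3-month eGFR, an unadjusted comparison leaves that predictable variation in the error term. The confidence interval is then wider than it needs to be, and a chance difference in severity between arms passes into the estimate.

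This matters more here than in a trial that could recruit further. The Discussion says that a larger trial was not feasible, that dropout or cross-over could leave the trial underpowered, and that a difference below 10 ml/min/1.73 m² could matter clinically. Baseline adjustment adds information without adding patients.

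There is also a question of designation. If the GLM turns out to contain both arm and day-0 eGFR, an adjusted and an unadjusted treatment effect will exist side by side, and the article does not say which one is primary.

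**Working it through.** **Inputs from the Statistics section:** difference 10 ml/min/1.73 m², SD 18, power 0.80, significance level 0.05 (taken as two-sided), 51 per arm before dropout, 55 per arm randomized.

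**Input not in the protocol:** the correlation r between day-0 and 3-month eGFR. It is assumed here and varied from 0.1 to 0.6.

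**Step 1: reproduce the planned size.** With the plain two-means formula,

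n per arm = 2 × (1.96 + 0.8416)² × (18/10)² = 50.9, so 51.

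This matches the protocol. The exact t-test calculation gives 51.8, so 52, a negligible difference. The formula contains no variance reduction for baseline. It is therefore consistent with an unadjusted comparison, though it does not prove that one is intended.

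**Step 2: power of the unadjusted test.** Exact two-sample t-test, 51 per arm, standardized difference 10/18 = 0.556: power 79.3%.

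**Step 3: power with day-0 eGFR as a linear covariate.** Residual SD = 18 × √(1 − r²). The equivalent unadjusted size per arm is 51/(1 − r²).

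| Assumed r | Residual SD | Power at 51 per arm | Equivalent unadjusted n per arm |
|---|---|---|---|
| 0 | 18.0 | 79.3% | 51 |
| 0.1 | 17.9 | 79.7% | 52 |
| 0.2 | 17.6 | 80.9% | 53 |
| 0.3 | 17.2 | 83.0% | 56 |
| 0.4 | 16.5 | 85.8% | 61 |
| 0.5 | 15.6 | 89.4% | 68 |
| 0.6 | 14.4 | 93.5% | 80 |

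At r = 0.2 the gain is 80.9 − 79.3 = 1.6 percentage points. At r = 0.5 it is 89.4 − 79.3 = 10.1 points.

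**Step 4: what a chance imbalance does to the unadjusted estimate.** A day-0 difference between arms of 1.96 standard errors shifts the 3-month difference by r × 18 × 1.96 × √(2/51). That is 2.1 ml/min at r = 0.3 and 3.5 ml/min at r = 0.5, against a target of 10. This is the same loss of precision seen from another side. The t-test's standard error already allows for it, so it is not a bias to be added on top.

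**Limit of the calculation.** The table assumes one linear covariate. With a dialysis indicator added, r² is replaced by the proportion of variance that day-0 eGFR and the indicator explain together, which is also unknown.

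**The case against.** The strongest reply is that the protocol never says the primary comparison is a t-test. The sentence is generic, a two-means sample size does not rule out an adjusted analysis, and a covariate list is commonly left to an analysis plan that is not shown. This stands in part. A reader might infer a firm commitment to an unadjusted primary test, and the text does not go that far. But the article does more than stay silent. It states a method for comparing groups, only that method fits this endpoint, and the sample size agrees with it.

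A second reply is that the GLM may already include arm and day-0 eGFR, and that the secondary endpoints use the day-0 value through change in plasma creatinine. Both are fair. Neither makes the adjusted comparison the primary one.

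A third is that the gain may be small. This stands: at r of 0.2 or below it is under 2 points, and function during the acute illness may track later function only loosely.

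Two further arguments are tempting but unsupported:

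- The Background says that steroid-treated patients in earlier studies "had higher baseline creatinine levels". Those cohorts were retrospective and not randomized. The imbalance reflects who was chosen for treatment, which randomization removes, and in a third cohort baseline renal function was comparable. It says nothing about chance imbalance in this trial.
- The Background also describes AIN as "requiring dialysis in 40% of cases". That is a literature figure, not the expected share on dialysis at entry to this trial, so it cannot be used to put a probability on a dialysis imbalance here.

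**Conclusion.** The point holds as a matter of efficiency and designation. The only named method that fits the primary comparison is unadjusted, the GLM is not assigned that role, and a pre-treatment covariate that is likely to be informative is already scheduled for every patient. At the planning values, adjustment raises power at 51 per arm from 79% to between about 80% (r = 0.1) and 93% (r = 0.6). The size depends entirely on a correlation that the protocol does not give, and at the low end the gain is negligible.

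A reader might go further and infer that the planned test is invalid or biased, or that the sample size is wrong. The protocol supports none of this. Under randomization the unadjusted comparison is unbiased and controls type I error, and 51 per arm follows from the stated inputs. This is an improvement worth making, not the correction of an error.

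**What to change.** Name as the primary intention-to-treat analysis a linear model (ANCOVA) of 3-month eGFR on randomized arm and day-0 eGFR. Score patients on dialysis at day 0 as 0, to match the rule at 3 months, and add an indicator for dialysis at day 0. Report the adjusted difference with its 95% confidence interval. Use the same model for 12-month eGFR and keep the unadjusted comparison as supportive.

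Say also whether the non-parametric fallback still applies to the primary endpoint. The zeros assigned for dialysis could trigger it, and as written it is unadjusted too. If a rank-based analysis is wanted, a baseline-adjusted version can be listed as a sensitivity analysis.

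The change affects analysis wording only. It needs no new data, no extra visits and no change to the sample size, and it should be fixed before any outcome is compared by arm.

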## Abbreviations

A1M: Alfa-1-mikrogolbulin
AIN: Acute interstitial nephritis
B2M: Beta-2-makroglobulin
BMP-7: Bone morphogenetic protein-7
eGFR: Estimated glomerular filtration rate
eCRF: Electronic Case report form
GLM: General linear model
IGFBP7: Insulin-like growth factor-binding protein 7
IL-18: Interleukin 18
KIM-1: Kidney injury marker 1
MCP-1: Monocyte chemotactic peptide-1
NAG: N-acetyl-beta-D-glucosaminidase
NGAL: Neutrophil gelatinase-associated lipocalin
PTH: Parathyroid hormone
TIMP-2: Tissue inhibitor of metalloproteinases-2
TGF-β1: Transforming growth factor-β1

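### The general linear model named for repeated measures handles missed visits or within-patient correlation poorly; a mixed model would do better in these secondary analyses

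*Protocol article*

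**What the plan says.** The Statistics section of the protocol article divides the methods by type of data. For comparisons at one time point, "Normally distributed variables are compared by unpaired t-test or one-way ANOVA", with non-parametric counterparts where normality fails. For longitudinal data, "Repeated measures are analyzed using a general linear model (GLM"). The abbreviation list gives "GLM: General linear model", so the generalized linear model is not meant. The article names no mixed model, within-patient covariance or rule for missed visits.

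The primary endpoint is a single value: "eGFR 3 months after inclusion (eGFR for patients on dialysis at 3 months is defined as" zero. On analysis sets, "The primary analysis will be performed as “intention to treat”, and the secondary analysis as “treated as".

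Table 1 schedules the repeated data. Creatinine and eGFR (Biochemistry A) are due at ten visits: days 0, 2 and 4, and weeks 1, 2, 4, 8, 12, 26 and 52. The biomarkers (Biochemistry C and spot urine B) are due at five: day 0 and weeks 1, 4, 12 and 52. SF-36 is due at four, as the Methods section confirms: "Quality of life is estimated with the SF-36 questionary which the patients fill in 4 times during the study period". Some loss is expected: "Anticipating dropouts, we estimate that 55 patients in each group are necessary".

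**The concern.** The label can be put into practice in two ways, and each has a weakness.

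- **One row per patient** (repeated-measures ANOVA or MANOVA). A patient with one missing modelled value is left out entirely, including the values that were recorded. This costs precision. If the reason for missing a visit relates to outcome and to arm, it can also bias the comparison.
- **One row per visit**, fitted as an ordinary linear model. Patients stay in, but repeated values from one patient are treated as independent, so standard errors and p-values are wrong.

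A likelihood-based mixed model avoids both, using data the trial already plans to collect. What is at stake is the precision and validity of the longitudinal results on renal function, quality of life and biomarkers.

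**Working it through.** **1. The plan's own sample size.** Inputs from the Statistics section: difference 10, SD 18, power 0.80, significance level 0.05 (taken as two-sided).

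n per group = 2 × (1.960 + 0.842)² × 18² / 10² ≈ 50.9, so 51. This matches the stated figure. Power is 80.1% at 51 per group and 83.0% at 55. The calculation is for two means at one time point, so it does not depend on the repeated-measures model.

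**2. The dropout allowance.** 1 − 51/55 = 7.3%. If dropout is the only source of missing data and stays within this allowance, 110 × 51/55 = 102 patients have complete data, however many visits are modelled.

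**3. Intermittent missed visits.** The article gives no rate. Assume a rate m per visit, independent across visits. The share of patients complete over k modelled visits is (1 − m)^k, and the expected number is 110 × (1 − m)^k.

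| Visits in the model | m = 2% | m = 5% | m = 10% |
|---|---|---|---|
| k = 2 (3 and 12 months) | 0.960 → 106 | 0.903 → 99 | 0.810 → 89 |
| k = 4 (SF-36) | 0.922 → 101 | 0.815 → 90 | 0.656 → 72 |
| k = 5 (biomarkers) | 0.904 → 99 | 0.774 → 85 | 0.590 → 65 |
| k = 10 (all creatinine/eGFR visits) | 0.817 → 90 | 0.599 → 66 | 0.349 → 38 |

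The loss depends mainly on which visits enter the model. Independence spreads missed visits over the most patients. If the same patients tend to miss several visits, fewer are lost.

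**4. Cost in precision.** Take nine post-baseline visits and m = 5%. The complete share is 0.95⁹ = 0.630, or 34.7 of 55 per arm. With SD 18, the standard error of the week-12 difference is 18 × √(2/55) = 3.43 with everyone and 18 × √(2/34.7) = 4.32 with completers only.

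A simulation of 300 trials, with an assumed correlation and values missing completely at random, agrees broadly:

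| m | Complete cases, SE | Likelihood model, SE |
|---|---|---|
| 2% | 4.03 | 3.67 |
| 5% | 4.60 | 3.45 |
| 10% | 5.13 | 3.40 |

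Simulation error in these standard errors is roughly 0.14 (3.43/√600) or more, so the drift within the last column is noise. The two methods gave similar average estimates (9.5 to 9.9, with 10 simulated). This is expected under completely random missingness, so the simulation shows a loss of precision and does not test for bias.

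**The case against.** **The deletion is inferred.** The article states no complete-case rule, software or data layout. It uses the same label for the regression of factors affecting the primary endpoint, so the term may simply name a family of models. The abbreviation list excludes the generalized linear model, but not every linear model with correlated errors. This stands, and so deletion should be described as what the usual procedure does, not as something the plan states. The point survives because both common ways of carrying out the sentence are weak.

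**This is detail for an analysis plan.** Covariance structure and estimation method normally are. The choice of model, however, is fixed in the article, and an analysis plan that used a mixed model would have to depart from or refine that wording.

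**No listed endpoint is tied to this model.** True. The secondary renal endpoints are mostly values or changes at 3 and 12 months and could each be tested separately. The ten-visit row is therefore the upper end of the loss, not the expected case.

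A reader might infer more than the documents support:

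- **That the primary result or the power is damaged.** The primary comparison is at one time point, and step 1 does not involve the repeated-measures model.
- **That intention to treat is breached.** The article ties that principle to the primary analysis, which is unaffected.
- **That the trial would analyse only 38 patients.** This needs an assumed 10% missed-visit rate, independence, and all ten visits in one model.
- **That the arms will be biased because controls skip days 2 and 4.** Nothing in the article says so. Withdrawal on developing an exclusion criterion, which includes advanced CKD and prednisolone intolerance, could link missing values to outcome or arm. The article does not say whether measurements stop at withdrawal, so bias remains a possibility only.

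**Conclusion.** The point holds for the repeated-measures analyses only, which are secondary or supportive. The named model either discards patients with any missing modelled visit or, on one row per visit, ignores within-patient correlation, and a better method is available on the same data.

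The size is uncertain because the article gives no missed-visit rate. Over the assumed range of 2% to 10%, the number of complete patients out of 110 runs from 106 to 89 with two visits modelled and from 90 to 38 with all ten. Under dropout alone, within the planned allowance, it is about 102. The loss is therefore small for a model of the two endpoint visits and becomes serious only when many visits are modelled with appreciable intermittent missingness. The change is worth making because it is cheap, but the trial's main conclusion does not depend on it.

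**What to change.** Replace the sentence on repeated measures with:

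> *Repeated measures are analysed with a linear mixed model (REML) using all available values from all randomised patients, with treatment, visit, treatment-by-visit and baseline value as fixed effects and a prespecified within-patient covariance (unstructured for the few endpoint visits, with a simpler structure as fallback when many visits are modelled). The 3- and 12-month contrasts are reported with 95% CI.*

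The fallback matters. An unstructured covariance over nine post-baseline visits has 9 × 10 / 2 = 45 parameters, to be estimated from at most 110 patients. For the two endpoint visits it has 3.

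State also how eGFR set to zero on dialysis enters the model, for example with a sensitivity analysis. A block of zeros strains the normality assumption, and the mixed model does not resolve this by itself.

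The cost is a sentence or two, standard software and slightly more analysis work, with no new data or patients. The downside is reliance on missing at random and on normality. Patients with no follow-up value still contribute nothing to the contrasts and should be counted by arm.

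### The observed distribution chooses the primary test, although scoring dialysis as 0 makes non-normality likely and the trial is sized on a mean difference; whether the SD of 18 counts those zeros is not stated

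*Protocol article*

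**What the plan says.** Under Endpoints (Primary), the outcome is eGFR 3 months after inclusion, and "eGFR for patients on dialysis at 3 months is defined as" zero.

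Under Statistics, the test depends on the distribution: "Normally distributed variables are compared by unpaired t-test or one-way ANOVA", and "Comparable non-parametric tests are used in case of non-normally distributed variables". The primary endpoint has no separate rule. A general linear model is mentioned for repeated measures and for factors affecting the primary endpoint, but not as the between-group comparison.

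The sample size, in the same section, is "based on a clinical relevant 10 ml/min/1.73m^2^ difference in renal function (eGFR, CKD-EPI) between groups at 3 months", with "a standard deviation of 18 ml/min, a power of 0.80 and a significance level of 0.05". The result is given as "This showed that 51 patients should be included in each group", and after an allowance for dropout "we estimate that 55 patients in each group are necessary and plan to randomize 110 patients".

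The Discussion says that the assumptions come from earlier retrospective studies. Nothing says whether the SD of 18 was computed with dialysis patients entered as 0. The Background indicates that some zeros are to be expected: "the risk of end stage renal disease requiring dialysis after biopsy proven AIN is 5–7" per cent.

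**The concern.** Three statements do not fit together. The endpoint definition places a cluster of values at zero, below the range of the other patients. The testing rule treats departure from normality as the trigger for a different test. The sample size assumes that the quantity of interest is a difference in means.

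If even a few patients per arm are on dialysis at 3 months, the trigger may well be met. The comparison then moves to a rank test, which addresses whether values in one arm tend to be higher than in the other. It does not estimate the 10 ml/min difference that the article calls clinically relevant. Which test and which effect measure are primary is settled only once the outcomes are visible, in a trial where treatment is known to clinicians and patients.

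There is a linked question about the SD. If 18 describes eGFR in patients off dialysis, the endpoint as defined can have a larger SD, and the stated power would then not apply to it.

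**Working it through.** **1. The plan's own figure.** Inputs from Statistics: difference 10, SD 18, power 0.80, significance level 0.05 (taken as two-sided).

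n per group = 2 × (1.960 + 0.842)² × 18² / 10² = 50.9, rounded up to 51. The stated 51 is reproduced, with power 0.801.

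**2. SD if 18 excludes the zeros.** Let p be the share scored 0 and m the mean eGFR off dialysis. Then

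SD² = (1 − p) × 18² + p(1 − p) × m²

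and, at 51 per group,

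power = Φ(10 / (SD × √(2/51)) − 1.96).

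The article gives neither p nor m at 3 months, so both are assumptions. Its nearest figures are 5–7% end-stage disease (Background) and mean eGFR of 42 and 24 ml/min at 24 months in steroid-treated and untreated patients of one retrospective cohort. Neither refers to 3 months. The 2%, the 10% and the mean of 50 have no source in the article and serve only to show the range.

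Worked example, p = 0.05 and m = 42: SD² = 0.95 × 324 + 0.0475 × 1764 = 307.8 + 83.8 = 391.6, so SD = 19.8 and power = 0.72.

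| p | m | SD | Power at 51 per group |
|---|---|---|---|
| 0% | any | 18.0 | 0.80 |
| 5% | 24 | 18.3 | 0.79 |
| 2% | 42 | 18.8 | 0.77 |
| 5% | 42 | 19.8 | 0.72 |
| 7% | 42 | 20.4 | 0.70 |
| 5% | 50 | 20.7 | 0.69 |
| 7% | 50 | 21.5 | 0.65 |
| 10% | 50 | 22.7 | 0.60 |

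These powers are for a comparison of means, with the overall difference, zeros included, held at 10. If 18 already includes the zeros, the 0% row applies whatever p is.

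**3. The test-choice rule.** Simulation with 51 per arm and 3,000 trials per setting. Off-dialysis eGFR is normal with SD 18, and a share p is set to 0 in each arm. The article does not name a normality check, so Shapiro-Wilk at 0.05 in each arm is assumed: if either arm fails, Mann-Whitney is used, otherwise the t-test. The gain is 10 ml/min among patients off dialysis.

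| p | m | Switch to rank test, null / gain | Type I error of the rule | Tests disagree, null / gain |
|---|---|---|---|---|
| 0% | 42 | 9% / 9% | 0.050 | 2% / 5% |
| 5% | 42 | 20% / 36% | 0.045 | 2% / 7% |
| 7% | 42 | 35% / 52% | 0.045 | 2% / 8% |
| 10% | 42 | 59% / 76% | 0.050 | 2% / 8% |
| 5% | 50 | 41% / 64% | 0.052 | 2% / 12% |
| 7% | 50 | 59% / 80% | 0.055 | 3% / 12% |
| 10% | 50 | 82% / 93% | 0.052 | 3% / 13% |

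With 5–10% zeros the primary test is therefore hard to predict in most of these settings. Where a real effect exists, the choice of test decides significance in roughly one trial in 8 to 14.

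**4. Whether data in hand could settle the SD.** The Time schedule reports 30 patients included. Even for normal data, an estimated SD of 18 from 30 patients has a 95% interval of 18 × √(29/45.7) to 18 × √(29/16.0), about 14 to 24. That interval covers every SD in the first table.

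**The case against.** The strongest reply is that the rule does little harm. Type I error is held, and the two tests rarely disagree under the null. When zeros are frequent the rank test is often the more powerful of the two, so the switch can help: with 10% zeros, a mean of 50 and an overall difference of 10, the rule as written has power of about 0.66, against 0.60 for the mean comparison by formula. All of this stands. It shows that the problem is neither false positives nor a poor rank test. It does not fix which question the primary analysis answers.

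A second reply is that a condensed article may leave the normality criterion and the name of the rank test to the analysis plan. That also stands, and neither omission is criticised here. The point is that the article states a data-dependent rule which, as written, covers the primary endpoint.

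On power, a reader might infer that the trial is underpowered or that its sample size is wrong. The document does not support either. The 51 per group is correct for the stated inputs, and the source of the SD cannot be seen. The loss is small if few patients are on dialysis or if eGFR off dialysis is low. The Discussion already concedes that the assumptions may be wrong, though it does not mention the zeros.

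**Conclusion.** The concern holds on the choice of test. Zero scoring makes non-normality likely, and the stated rule then leaves the primary test and effect measure to the observed data, although the trial is sized on a mean difference. With 5–10% zeros and a true gain, the two tests disagree on significance in about 7–13% of simulated trials (about 2% under the null), with type I error near 0.05. These rates rest on the assumed zero shares, means of 42–50, and a Shapiro-Wilk trigger.

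The SD is an open question, not a demonstrated error. If 18 counts dialysis patients as 0, the power of 0.80 stands. If not, the conditional power for a mean comparison is about 0.77–0.79 at the mild end, 0.65–0.72 with 5–7% zeros and a mean of 42–50, and 0.60 with 10% zeros and a mean of 50.

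**What to change.** Before outcome data are examined, name one primary analysis that applies whatever the distribution. One suitable choice is the mean difference in 3-month eGFR, with dialysis scored 0, adjusted for day-0 renal function and with robust standard errors. State how patients on dialysis at day 0 are coded, because the article defines the zero only at 3 months. Report the rank test as a sensitivity analysis.

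State whether the SD of 18 counts dialysis patients as 0. If it does not, give the power for 51 per group as a conditional range like the one above. The sample size need not rise; the Discussion says that a larger trial was not feasible. A pooled SD from the roughly 30 patients included so far is too imprecise to replace this statement.

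The cost is a few sentences of analysis wording and one check of the SD's source. There are two downsides: a mean comparison can have less power than the rank test when zeros are frequent, and the restated power may look less favourable than 0.80.
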